| Solicited local and systemic adverse events (AEs) for 7 days after vaccine. Via E-diary     |                                               |                   |         |         | X (7 days)              |         |         |              |
| Unsolicited local and systemic adverse events (AEs) for 28 days after vaccine . Via E-diary |                                               |                   |         |         | X           |         |         |              |
| Unsolicited SAEs                                                                            |                                               | X                 |         |         |                         |         |         |              |
| Medically-attended adverse events (MAAEs)                                                   |                                               | X                 |         |         |                         |         |         |              |
| Immune response evaluation                                                                  |                                               | X                 | X       | X       | X                       | X       | X       | X            |

Note: If subjects in Group 2 are not crossed over, the visits will be the same as the groups 1.

1. Temperature, blood pressure and heart rate

2. Lab determination could be performed either at screening visit or randomization

3. Two days per week

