**Participants with COVID19-like signs and symptoms**

| Procedure                                                                                                | Symptoms | Confirmation | Early Follow up | Late Follow up |
|----------------------------------------------------------------------------------------------------------|----------|--------------|-----------------|----------------|
| Day $\pm$ window                                                                                         | Day 1-2  | Day 2-5      | Day 6 to 28     | Day 29 $\pm$ 7 |
| Site to contact participant if COVID19 signs or symptoms are recorded in the e-Diary                     | X        |              |                 |                |
| Case evaluation                                                                                          | X        |              |                 |                |
| Nasal swab sample                                                                                        |          | X            |                 |                |
| Humoral immunity                                                                                         |          | X            |                 | X              |
| Biomarker RNAseq                                                                                         |          | X            |                 | X              |
| Vital signs, including pulse oximetry                                                                    |          | X            |                 | X              |
| Symptoms of infection, including highest body temperature over the last 24 hours measured by participant |          | X            |                 | X              |

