| To assess the humoral immune response against viral variants of SARS-CoV-2, 14 and 28 days after a dose of COMIRNATY in subjects that received a previous single dose of VAXZEVRIA.                                            | 
-Serological response to vaccination (antibodies against SARS-CoV-2 spike protein) as measured by immunoassay at 3, 6 and 12months after the boost dose.
 
- SARS-CoV-2 neutralization as measured by virus neutralization assay at 3, 6 and 12 months after the boost dose.
                                                                                                                                                                                                                 |
| Secondary efficacy objective                                                                                                                                                                                            |                                                                                                                                                                                                                                                                                                                                                                                                                                                                                                          |
| To assess the occurrence of symptomatic molecularly confirmed COVID-19 and severity of COVID-19 signs and symptoms after the administration of a dose of COMIRNATY in subjects that received a prior single dose of VAXZEVRIA. | 
- The number of participants with molecularly confirmed COVID-19.
 
- Presence and severity of COVID-19 signs and symptoms as measured by Symptoms of Infection with Coronavirus-19 (SIC).
                                                                                                                                                                                                                                                                                                   |

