## **4. Study Design**

### **4.1. Overall Design**

This is a randomized, non-blinded, controlled, adaptive, multicenter, Phase II study in subjects aged more than 18 years and in good health or stable clinical situation that have received a previous single dose of VAXZEVRIA.

This is a phase 2 adaptive trial developed for evaluating the immunogenicity of a dose of COMIRNATY after a previous single dose with VAXZEVRIA. A stratification will be made for the following factors: site of vaccination, sex and age. This protocol allows to test the immunogenicity and safety of a heterologous vaccination strategy after a single dose of VAXZEVRIA.

Subjects will be randomized to immediately receive or not dose of COMIRNATY in a proportion of 2:1.

If primary analysis at 14 days confirms the starting hypothesis, subjects randomized to no vaccination will be considered for administration of one dose of COMINARTY at day 28th according to Public Health Department of the Ministry of Health recommendations on heterologous vaccination. If vaccinated, subjects will be followed at the time points defined in the flowchart.

In case the primary analysis does not confirm the starting hypothesis, subject will be followed without administration of COMINARTY.

In case Public Health Department gave instructions to give the second dose of VAXZEVRIA to those subjects having received the first dose, subject will be followed as indicated in flowchart of Group 2.

Other heterologous vaccination strategies could be incorporated if deemed necessary for public health reasons. This could include the use of different boost strategies including those already marketed vaccines for comparative assessment of their safety and efficacy on SARS-CoV-2 and its variants.

The different intervention arms planned (and its corresponding control arm) can be carried-out in different trial sites, thus not all trial sites must participate in all arms.

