## 8.2. Efficacy assessments

Occurrence of confirmed COVID-19 is defined as the presence of a documented positive SARS-CoV-2 test performed within a healthcare facility. Classification of severity will be based on the highest degree of severity during the observation period.

In general, adults with SARS-CoV-2 infection can be grouped into the following severity of illness categories. However, the criteria for each category may overlap or vary across clinical guidelines and clinical trials, and a patient's clinical status may change over time.

- Asymptomatic or Presymptomatic Infection: Individuals who test positive for SARS-CoV-2 using a virologic test (i.e., a nucleic acid amplification test or an antigen test) but who have no symptoms that are consistent with COVID-19.
- Mild Illness: Individuals who have any of the various signs and symptoms of COVID-19 (e.g., fever, cough, sore throat, malaise, headache, muscle pain, nausea, vomiting, diarrhea, loss of taste and smell) but who do not have shortness of breath, dyspnea, or abnormal chest imaging.
- Moderate Illness: Individuals who show evidence of lower respiratory disease during clinical assessment or imaging and who have saturation of oxygen (SpO2)  $\geq 94\%$  on room air at sea level.
- Severe Illness: individuals hospitalized needing oxygen by NIV or high flow, re-breather mask.
- Critical Illness: Individuals who have respiratory failure, septic shock, and/or multiple organ dysfunction.

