### **9.3.3. Secondary endpoint(s) analysis**

Secondary immunogenicity endpoints (serological response and neutralizing antibodies at each time point) between the two arms will be tested by one-tailed t-test assuming symmetric distribution of lognormal transformation. Geometric means will be calculated as the mean of the assay results after making the logarithm transformation and then exponentiating the mean to express results on the original scale. One-sided 95% CIs will be obtained by taking natural log transforms of concentrations/titers, calculating the 95% CI with reference to the t-distribution, and then exponentiating the confidence limits. In other case, Mann-Whitney-Wilcoxon test will be used.

For secondary efficacy objectives, the absolute and relative frequencies of individuals with molecularly confirmed COVID-19 and SIC will be compared through the two-tailed chi-square test and alpha error equal to 0.05.

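### The COVID-19 comparison has no time limit despite a possible Day-28 crossover, and the e-Diary that triggers case work-up is not scheduled alike in the two arms before it

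*Protocol*

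**What the plan says.** **Test and endpoint.** Section 9.3.3 states that "absolute and relative frequencies of individuals with molecularly confirmed COVID-19 and SIC will be compared through the two-tailed chi-square test", at an alpha of 0.05. The endpoint in Table 3.1 is "The number of participants with molecularly confirmed COVID-19". Neither place gives a time frame, and the Synopsis does not either. The immunogenicity endpoints and most safety endpoints do carry time points.

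**Case definition.** Table 3.1 gives the objective as "To assess the occurrence of symptomatic molecularly confirmed COVID-19". Section 8.2 says: "Occurrence of confirmed COVID-19 is defined as the presence of a documented positive SARS-CoV-2 test performed within a healthcare facility". It grades severity over an observation period of unstated length, and its first category is infection without symptoms.

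**Crossover.** Section 4.1 says that, if the Day-14 analysis confirms the hypothesis, "subjects randomized to no vaccination will be considered for administration of one dose of COMINARTY at day 28th", depending on public health recommendations. It also allows for an instructed second dose of VAXZEVRIA. Follow-up is one year, with the last visit at Day 360.

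**Case finding.** The section 1.2 table for participants with COVID-19-like symptoms begins with "Site to contact participant if COVID19 signs or symptoms are recorded in the e-Diary". The e-Diary appears in the visit charts only in two adverse-event rows: a 7-day solicited row and "Unsolicited local and systemic adverse events (AEs) for 28 days after vaccine . Via E-diary". Both are marked at V1 (Day 0) in Group 1 and at V4 (Day 28) in the crossover chart for Group 2.

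**The concern.** A between-arm comparison of cumulative cases needs a period in which the arms differ in treatment and cases are found in the same way. The plan secures neither.

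If controls cross over, most of their follow-up is vaccinated time, so a year-long count compares two largely vaccinated groups. The period that keeps the randomised contrast, Days 0-28, is also the one in which the scheduled trigger for COVID-19 work-up runs in Group 1 and not in Group 2. The SAP can add a cut-off. It cannot recover symptom entries that controls were never asked to make.

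The objective and section 8.2 also count different events, so two analysts could report different numbers of cases from the same data.

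**Working it through.** The Protocol gives no attack rate, efficacy or power for this comparison, so there is no planned figure to reproduce. The rates below are assumptions.

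**1. Share of control time after crossover.** Inputs: dose at Day 28 (section 4.1) and last visit at Day 360 (section 1.2). (360 - 28)/360 = 332/360 = 0.92.

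**2. Dilution if the count runs to Day 360.** Assume a constant hazard h in unvaccinated time, a hazard of h(1 - VE) from the day of dosing, and equal detection. With 28-day control risk r, h = -ln(1 - r)/28.

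- Group 1: p1 = 1 - exp[-360 h(1 - VE)]
- Group 2, crossed over: p2 = 1 - exp[-h(28 + 332(1 - VE))]
- Apparent VE = 1 - p1/p2

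Example with r = 1% and VE = 80%: p1 = 0.026 and p2 = 0.033, and the unrounded values give an apparent VE of 23%. At low risk the formula reduces to 1 - 360(1 - VE)/[28 + 332(1 - VE)]. For VE = 80% this is 1 - 72/94.4 = 24%.

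| True VE | Apparent VE, crossover at Day 28 (r = 0.5% to 2%) |
|---|---|
| 50% | 7% |
| 70% | 15% |
| 80% | 23% to 24% |
| 90% | 41% |

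Approximate power with 400 and 200 participants, two-sided 0.05, over the same ranges:

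- all follow-up with crossover: 4% to 23%
- all follow-up without crossover: 43% to over 99%
- Days 0-28 only: 10% to 61%

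**3. e-Diary coverage as scheduled.**

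| Period | Group 1 | Group 2, crossed over |
|---|---|---|
| Days 0-28 | yes | no |
| Days 28-56 | no | yes |
| After Day 56 | no | no |

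Apart from the 3-day window around V4, no scheduled period has the diary running in both arms. The note that controls who do not cross over follow the Group 1 visits does not settle this, because a diary that runs after vaccination has no start date in an unvaccinated participant. The crossover decision also comes after the Day-14 result, when the first two weeks have passed.

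**4. What unequal detection alone could do in Days 0-28.** If Group 2 cases are found at a fraction s of the Group 1 rate, apparent VE = 1 - (1 - VE)/s.

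| s (assumed) | True VE 80% | True VE 50% |
|---|---|---|
| 1 | 80% | 50% |
| 0.75 | 73% | 33% |
| 0.5 | 60% | 0% |
| 0.25 | 20% | -100% |

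This shows sensitivity to the diary asymmetry taken by itself. It does not estimate the net bias.

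**5. Cases expected in the 28-day window.** With 200 controls and an assumed 28-day risk of 0.1% to 2%: 200 x 0.001 = 0.2 and 200 x 0.02 = 4.

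**The case against.** **Section 9 is only a summary, and the SAP can set a window, censor at crossover and substitute an exact test.** This stands for those three items. It does not answer the unequal diary schedule, which is a matter of data collection.

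**The diary is not the only route to a case.** This stands. Both arms are asked about adverse events and well-being at Days 7, 14 and 28 (section 8), both charts mark SAEs and MAAEs from V1, and any positive test in a healthcare facility counts in either arm. Crossed-over controls also have a PCR at V4 that Group 1 does not have, which works the other way. A reader might infer that cases are sought in one arm only, or that the bias must run against the vaccine. The Protocol supports neither.

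**The diary rows concern adverse events.** That they also carry COVID-19 symptoms is inferred from the work-up table, since no other diary use is scheduled. The Group 1 diary is also not a daily record for 28 days, because unsolicited entries are made on two days per week.

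**Sparse counts.** A reader might infer that chi-square fails as written because expected counts fall below 5. The counts of 0.2 to 4 belong to the 28-day window. The same rates extended to 360 days without crossover give about 2.6 to 46 control cases, so sparsity in the unrestricted test depends on the rate.

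**SIC and antigen tests.** A reader might infer that vaccine reactions would be counted as COVID-19 through SIC, or that antigen tests confirm a case. The SIC items are not listed, and symptoms of infection are scheduled only in the suspected-case pathway. Antigen tests appear only in the description of the asymptomatic category, while the endpoint and the analysis both say molecularly confirmed.

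**Conclusion.** The point holds in three parts.

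- **No time limit.** If controls cross over, 92% of their follow-up is vaccinated time and the contrast is pulled strongly toward the null: a true efficacy of 80% would appear as about 23% to 24%. This depends on the crossover, which is conditional, and on a constant hazard, full effect from the day of dosing and no waning.
- **Unequal case finding in Days 0-28.** The work-up trigger is scheduled in Group 1 and not in Group 2. Detection in controls is unequal, not absent, and neither the size nor the sign of the net bias can be fixed from the Protocol.
- **Mismatched case definition.** Section 8.2 accepts any documented positive test and includes infection without symptoms. The objective requires symptomatic, molecularly confirmed disease.

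This is a secondary comparison with no power claim. The Day-14 primary analysis precedes any crossover and is not affected. The change should still be made, because the plan attaches a p-value to a contrast that would be hard to interpret.

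**What to change.** 1. **Section 1.2:** run the same e-Diary COVID-19 symptom prompts in both arms from Day 0, and say so in both visit charts.
2. **Section 9.3.3:** limit the between-arm comparison to cases with onset from randomisation to Day 28, or to an earlier control-arm dose, ending before any V4 PCR result counts. Describe later cases by time since dose.
3. **Test:** use an exact test with an exact confidence interval, because few cases are likely in that window.
4. **SIC:** summarise it in confirmed cases.
5. **Section 8.2:** match the case definition to the objective (symptoms plus a positive molecular test), and list other positives separately.

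The cost is a change of wording and a small diary burden for about 200 controls over 28 days. Power stays low, at about 10% to 61% under the assumptions above, so the estimate and its interval will matter more than the p-value. Where controls have already passed Day 28, the prompts cannot be added afterwards. Items 2 to 5 still apply, and the unequal case finding should be reported as a limitation.

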### **9.3.4. Exploratory/subgroup analysis**

No subgroup analysis will be carried out.

### **9.3.5. Safety analyses**

Safety endpoints include serious adverse events (SAEs) leading to study treatment discontinuation and death. SAEs will be coded using the current version of the Medical Dictionary for Regulatory Activities (MedDRA). SAEs leading to study treatment discontinuation and death will be summarized with absolute and relative frequencies (%) with 95% confidence intervals (CIs). More details on the statistical analysis will be provided in the SAP.

## **9.4. Interim Analysis**

No formal interim analysis for efficacy will be done. However, an independent data monitoring committee consisting of independent scientists not otherwise involved in the study has been appointed and will review the data regularly during the study for safety and scientific integrity and will make recommendations to the sponsor regarding the stopping of an intervention for harm or for futility. The frequency of the committee data review meetings and other aspects such as stopping rules will be detailed in a separate charter depending on the safety profile of the study intervention(s).

## **9.5. Sample Size Determination**

Sample size calculation for a log-transformed outcome measure (Wolfe R, Carlin JB. Sample-size calculation for a log-transformed outcome measure. *Control Clin Trials*. 1999 Dec;20(6):547-54. doi: 10.1016/s0197-2456(99)00032-x. PMID: 10588295) has been performed to assess the humoral immune response against SARS-CoV-2 14 days after dose of COMIRNATY in subjects that received a prior single dose of VAXZERIA, as compared with no dosing. Sample size to obtain will be 600 participants divided in 400 in arm1 and 200 in arm2 (2:1 randomization ratio): we assume that: a) increase in antibodies titer would be at least x1.35 in subjects receiving the dose of COMIRNATY G(Y1) in relation with those not receiving it G(Y2); b) a coefficient of variation equal to 1.2 or 1.0 and similar between arms, c) a 80% statistical power and alpha equal to 0.01 for one side test ( $H1: G(Y1)/G(Y2) > 1$ ). See table below for different assumptions in coefficient

of variation and  $G(Y1)/G(Y2)$ . The planned sample size is also considered appropriate to evaluate safety endpoints.

The sample size will be increased by 15% of the participants being non-evaluable.

| Case | alfa | beta | 2:1 | Coef. Var | $G(Y1)/G(Y2)$ | VAXZERIA group (n=) | COMIRNATY group (n=) |
|------|------|------|-----|-----------|---------------|---------------------|----------------------|
| 2    | 0.01 | 0.2  | 2   | 1.2       | 1.35          | 173.506             | 347.012              |
| 3    | 0.01 | 0.2  | 2   | 1.2       | 1.40          | 138.026             | 276.052              |
| 4    | 0.01 | 0.2  | 2   | 1.2       | 1.45          | 113.186             | 226.372              |
| 5    | 0.01 | 0.2  | 2   | 1.2       | 1.50          | 95.050              | 190.100              |
| 7    | 0.01 | 0.2  | 2   | 1.1       | 1.35          | 154.248             | 308.496              |
| 8    | 0.01 | 0.2  | 2   | 1.1       | 1.40          | 122.706             | 245.412              |
| 9    | 0.01 | 0.2  | 2   | 1.1       | 1.45          | 100.623             | 201.247              |
| 10   | 0.01 | 0.2  | 2   | 1.1       | 1.50          | 84.500              | 169.000              |
| 12   | 0.01 | 0.2  | 2   | 1.0       | 1.35          | 134.827             | 269.653              |
| 13   | 0.01 | 0.2  | 2   | 1.0       | 1.40          | 107.256             | 214.513              |
| 14   | 0.01 | 0.2  | 2   | 1.0       | 1.45          | 87.954              | 175.908              |
| 15   | 0.01 | 0.2  | 2   | 1.0       | 1.50          | 73.861              | 147.722              |

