| Participant Population:                             | 
Inclusion criteria
 
 
1. Adult subjects (18 years old) having received prior VAXZEVRIA vaccination between 8 and 12 weeks before the screening visit.
 
2. Participants must provide consent indicating that he or she understands the purpose, procedures and potential risks and benefits of the study, and is willing to participate in the study.
 
3. Subjects in good health or stable clinical situation.
 
4. Participant is willing and able to adhere to the procedures specified in this protocol.
 
 
Exclusion criteria
 
 
1. Participant has a clinically significant acute illness (this does not include minor illnesses such as diarrhea or mild upper respiratory tract infection) or temperature <math>\geq 38.0^{\circ}\text{C}</math> within 24 hours prior to the planned dose of study vaccine.
 
2. Participant has a known or suspected allergy or history of anaphylaxis or other serious adverse reactions to COMIRNATY excipients.
 
3. Subjects with any contraindication to the administration of COMIRNATY, included pregnancy.
 
4. Subjects with prior documented COVID19 since VAXZEVRIA vaccination.
 
5. Subjects have symptoms or signs compatible with COVID19.
 
6. Subjects participating in a clinical trial in the last three months.
 
7. Any condition or situation precluding or interfering the compliance with the protocol.
 
 
Number of participants:
 
The total planned number of patients to be included is 600 (400 in COMINARTY arm and 200 in no vaccination arm).
 |

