#### 9.3.2. Primary endpoint(s) analysis

The immune response measured by immunoassay 14 days after randomisation between the two arms will be tested by one-tailed t-test assuming symmetric distribution of lognormal transformation. Geometric means will be calculated as the mean of the assay results after making the logarithm transformation and then exponentiating the mean to express results on the original scale. One-sided 95% CIs will be obtained by taking natural log transforms of concentrations/titers, calculating the 95% CI with reference to the t-distribution, and then exponentiating the confidence limits. In other case, Mann-Whitney-Wilcoxon test will be used.

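### The sample size table in 9.5 was computed at one-sided 0.005, not the stated one-sided 0.01, and the confidence level in 9.3.2 does not match the stated alpha

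*Protocol*

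**What the plan says.** Section 9.1 sets a one-sided alternative for the day-14 geometric mean ratio of COMIRNATY to no dose. Section 9.5 sizes the trial for that comparison. It assumes a ratio of 1.35 ("increase in antibodies titer would be at least x1.35 in subjects receiving the dose of COMIRNATY"), variability given as "b) a coefficient of variation equal to 1.2 or 1.0 and similar between arms", and "c) a 80% statistical power and alpha equal to 0.01 for one side test". The largest case in its table reads "2 | 0.01 | 0.2 | 2 | 1.2 | 1.35 | 173.506 | 347.012"; the last two figures are the control and COMIRNATY arms. The alpha column shows 0.01 without saying whether it is one-sided or two-sided.

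The text of 9.5 gives the total as "Sample size to obtain will be 600 participants divided in 400 in arm1 and 200 in arm2 (2:1 randomization ratio" and adds: "The sample size will be increased by 15% of the participants being non-evaluable". The synopsis also fixes the total: "The total planned number of patients to be included is 600".

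Section 9.3.2 plans a one-tailed t-test on log titres and gives no significance level for it. On confidence limits it says: "One-sided 95% CIs will be obtained by taking natural log transforms of concentrations/titers".

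**The concern.** The sample size text, its table and the primary analysis should describe one test at one level. Here the table does not follow from the text above it, and the only confidence level in 9.3.2 does not correspond to the only alpha stated for the primary test.

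Two things depend on this. The first is the stated power, which is wrong for the stated test. The second is the criterion for success. Under the synopsis and sections 4.1 and 6.1.2, confirmation of the starting hypothesis at day 14 is one condition for considering COMIRNATY in the control arm at day 28. In an open-label trial with a rapid readout, the level at which the hypothesis counts as confirmed should be beyond dispute before data are seen.

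**Working it through.** **Inputs (section 9.5).** Ratio 1.35, so the log difference is ln 1.35 = 0.3001 and its square is 0.09006. Coefficient of variation 1.2, so the log-scale variance is ln(1 + 1.2²) = ln 2.44 = 0.8920 and the SD is 0.9445. Power 80%, z = 0.8416. Allocation 2:1.

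**Formula.** With twice as many participants on COMIRNATY as in control, the normal approximation on the log scale gives

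n(control) = 1.5 × ln(1 + CV²) × (z_alpha + 0.8416)² / (ln ratio)².

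**Step 1: reproduce the table.** With z_alpha = 2.5758, case 2 gives 1.5 × 0.8920 × 11.679 / 0.09006 = 173.506, and twice that is 347.012. Both match the printed figures. The other 11 rows also match to three decimals. Solving each row for z_alpha gives 2.5758 every time, which is one-sided 0.005 or two-sided 0.01.

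**Step 2: apply the stated test.** With z_alpha = 2.3263 (one-sided 0.01), case 2 gives 1.5 × 0.8920 × 10.036 / 0.09006 = 149.1, and twice that is 298.2. No row matches at this level; every printed figure is 16.4% too large (11.679 / 10.036 = 1.164).

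| Case 2 | z_alpha | Control | COMIRNATY | Total evaluable |
|---|---|---|---|---|
| Printed table | 2.5758 | 173.5 | 347.0 | 520.5 |
| One-sided 0.01, as stated | 2.3263 | 149.1 | 298.2 | 447.3 |

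**Step 3: where 600 comes from.** 173.5 × 1.15 = 199.5 and 347.0 × 1.15 = 399.1, in total 598.6. So 600 (400 + 200) is case 2 with the 15% already added. A 15% loss from 600 leaves 510 evaluable (340 + 170). Dividing by 0.85 instead of multiplying by 1.15 would have given 520.5 / 0.85 = 612.

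**Step 4: power of the planned trial.** With 340/170 evaluable, the standard error of the log ratio is 0.9445 × √(1/340 + 1/170) = 0.0887, and the noncentrality is 0.3001 / 0.0887 = 3.38. Noncentral t power at one-sided 0.01 is about 85%. With all 400/200 evaluable it is about 91%.

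**Step 5: what the confidence level in 9.3.2 would imply.** A lower one-sided 95% limit above 1 is a one-sided test at 0.05, and 0.05 / 0.01 = 5. With 340/170 evaluable and a log-scale SD of 0.9445, the smallest observed ratio that passes is exp(t × 0.0887):

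| One-sided level | t (508 df) | Smallest passing ratio | Power at ratio 1.35 |
|---|---|---|---|
| 0.01 | 2.334 | 1.23 | about 85% |
| 0.05 | 1.648 | 1.16 | about 96% |

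Observed ratios between about 1.16 and 1.23 pass at 0.05 and fail at 0.01.

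**The case against.** A reader might infer that three thresholds compete for the decision (0.005, 0.01 and 0.05), with a tenfold spread in type I error. The protocol does not support that. A sample size table is not a decision rule, and no section plans a test at 0.005 or a two-sided primary test. Sections 9.1, 9.3.2 and 9.5 all describe a one-sided one. The table does not label sidedness, so its level is inferred from the arithmetic.

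Nor does 9.3.2 say that the 95% limit decides success. Its sentence describes how limits are obtained for titres, and it does not say that they apply to the ratio. The only alpha stated for the primary test is one-sided 0.01; the 0.05 in 9.3.3 belongs to the chi-square test for secondary efficacy. The limits may be meant for reporting only, and further detail is deferred to a SAP that is not at hand.

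A reader might also take the 15% sentence to mean 690 participants, or a trial that is too small. The synopsis and 9.5 both fix 600, Step 3 shows that the increase is already in it, and the gap between 600 and 612 is immaterial given the surplus in Step 4.

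Finally, the practical reach is narrow. An observed ratio at the design value of 1.35 passes at either level, and vaccination of controls is only considered, subject to public health recommendations.

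All of this stands, and it limits the point. It does not remove it: the table still contradicts the text above it, the 80% is still not the power of the stated test, and nothing in the protocol says how a one-sided 95% limit relates to an alpha of 0.01. A SAP could not follow all three as written.

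**Conclusion.** The table in 9.5 is wrong for the test that 9.5 states. It overstates the requirement by 16.4% in every row, in case 2 by about 73 evaluable participants (520.5 against 447.3). The error is on the safe side: at one-sided 0.01 the trial has about 85% power with 510 evaluable, so power is not at risk.

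The mismatch between the stated alpha and the confidence level in 9.3.2 is a separate and conditional problem. It raises the type I error from 0.01 to 0.05 only if the 95% limit is used to judge confirmation. In that event the conclusion changes only for observed ratios of about 1.16 to 1.23.

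The table result rests on the normal approximation, which all 12 rows confirm. The power and the ratios assume a coefficient of variation of 1.2, 340/170 evaluable participants and a t-test on log titres; the power also assumes a true ratio of 1.35.

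**What to change.** 1. State one-sided alpha 0.01 for the primary test in 9.1, 9.3.2 and 9.5.
2. In 9.3.2, pair it with a one-sided 99% lower limit for the geometric mean ratio, or state that the 95% limits are descriptive and do not decide whether the hypothesis is confirmed.
3. In 9.5, recompute the table with z = 2.326, or keep the figures and say in the text that the trial was sized conservatively at one-sided 0.005. A bare label of two-sided 0.01 is not enough, because the table would then describe a test other than the planned one.
4. Reword the 15% sentence to say that 600 already includes the allowance, and that 510 evaluable participants give about 85% power at one-sided 0.01 with a coefficient of variation of 1.2 and a ratio of 1.35.

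The cost is a few sentences and at most one recomputed table. Enrolment does not change.
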